### Additional analyses {20b}

Based on the clinical observation indexes and shoulder joint MRI and musculoskeletal ultrasound imaging data before and after treatment of a total of 320 patients collected in the study, a multi-factor correlation analysis will be performed using subgroup analysis, sensitivity analysis, and logistic regression so that the following can be determined.1.1Whether there was a positive correlation between the shoulder joint active and passive mobility, pain and the data of the staging, and degree of rotator cuff injury characterized by shoulder MRI and musculoskeletal ultrasound imagining. During the MRI analysis, the primary analysis indicator used to assess the rotator cuff injury was the Ellman classification system [58], which takes into account both the tear's location and depth. There are two types of tears: partial-thickness tear (P) and full-thickness tear (F). For partial-thickness tears, they are categorized as follows: A: articular, B: bursal, C: intratendinous, and further graded as Grade 1 (<3 mm), Grade 2 (3−6 mm), and Grade 3 (>6 mm). For full-thickness tears, they are categorized based on the affected muscles: (A) supraspinatus, (B) infraspinatus, (C) teres minor, and (D) subscapularis and graded as Grade 1 (small, <2 cm), Grade 2 (large, 2–4 cm), Grade 3 (massive, >5 cm), and Grade 4 (cuff arthropathy). Since one of the most common complications of a rotator cuff tear is supraspinatus muscle atrophy [59], and fat infiltration is correlated with the severity of the rotator cuff tear [60], the secondary indicators will be Goutallier’s classification [61, 62] on fatty degeneration of cuff muscles and the Thomazeau classification of supraspinatus muscle atrophy [63]. Our designated medical professional will be responsible for interpreting all the MRI findings and comparing MRI images in later visits. This ensures integrity and accuracy in data analysis, minimizing the potential errors in data interpretation.1.2The type and the degree of rotator cuff injury for which the MUA is suitable, and the best indication for the maneuver.1.3Whether there is an increase in the degree of rotator cuff injury after MUA and to verify the safety of MUA on patients with rotator cuff injury.

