### Sample size {14}

The total effective rate is the primary outcome parameter. This is based on the efficacy of previous studies on MUA [56] and intra-articular steroid injection [57] in the treatment of FS. The sampling ratio for the treatment and control groups is 1:1, and the number of test subjects required for each group sets as *n*, using a two-sided test. πT and πC are the reference values for the efficacy of previous studies on MUA and steroid substance shoulder cavity injection for FS, respectively [56, 57], setting πT = 0.862 and πC = 0.428. Based on these parameters, we calculated a sample size of 160 subjects per group with a power of 80%, alpha 0.05, and a 10% drop out rate.

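### Item 1.2 of the additional analyses asks which cuff lesions suit MUA but frames the answer as a correlation analysis; suitability needs an arm-by-baseline-lesion contrast, labelled exploratory

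*Protocol article*

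**What the plan says.** Additional analyses {20b} states the method in its lead sentence: "a multi-factor correlation analysis will be performed using subgroup analysis, sensitivity analysis, and logistic regression so that the following can be determined". The data are clinical indices together with "imaging data before and after treatment of a total of 320 patients", that is, both arms together. Three items follow. Item 1.2 is the "type and the degree of rotator cuff injury for which the MUA is suitable, and the best indication for the maneuver". Item 1.3 asks whether the cuff injury increases after MUA.

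Under item 1.1 the Ellman system is the primary way of reading the MRI: partial-thickness tears by three locations and three grades, full-thickness tears by four muscles and four grades.

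Statistical methods, Outcomes {20a}, uses logistic regression to relate treatment to efficacy and says that treatment effects will carry 95% confidence intervals. Neither section names a comparison of the treatment effect across baseline lesion classes. The allocation section stratifies randomisation by site only.

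**The concern.** To say for which lesion MUA is suitable, in a trial of MUA against injection, is to say how the difference between the arms changes with the lesion present before treatment. The named framework is correlation. Correlating lesion with outcome shows which lesions go with a poor result. It does not show whether injection would have done any better in those shoulders.

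The matter has practical weight. The background section says that many physicians already withhold MUA when MRI shows a cuff injury or tear. Of all the additional analyses, a statement about indication is the one most likely to reach practice. If a lesion that does badly under both treatments is reported as unsuitable for MUA, that habit is reinforced without support from the randomised comparison. The lead sentence also promises to determine the answer, which is more than the named methods can deliver in an additional analysis.

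**Working it through.** **Inputs.** From Sample size {14}: "setting πT = 0.862 and πC = 0.428", "with a power of 80%, alpha 0.05, and a 10% drop out rate", and 160 per group. Evaluable per arm: 160 × 0.9 = 144. *Assumed*, because the documents give no such figures: a two-level baseline lesion (A, B), with B in 25–50% of patients and a control response in B of 0.228 (20 points below 0.428).

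**The plan's own figure.** The plan gives no figure for item 1.2. Its only calculation is the 160 per group. The usual two-sided formula gives n = [1.96√(2 × 0.645 × 0.355) + 0.8416√(0.862 × 0.138 + 0.428 × 0.572)]² / 0.434² = 17.9, so 18 per group, and 18/0.9 = 20 with dropout. The 160 is therefore not reproduced. That is a separate matter; here 160 is used only to fix the number of patients.

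**1. A correlation cannot identify suitability.**
- Planning odds ratio: (0.862/0.138)/(0.428/0.572) = 8.35.
- Apply it in B: odds 0.228/0.772 × 8.35 = 2.47, so the MUA response in B is 0.711.
- Benefit of MUA: 0.862 − 0.428 = 43.4 points in A; 0.711 − 0.228 = 48.3 points in B. B is a poor-prognosis lesion in which MUA works as well as elsewhere.
- MUA patients alone show 0.862 in A and 0.711 in B. They would show the same if the control rate in B were also 0.711, that is, with no benefit in B.
- Pooled over arms, B shows (0.711 + 0.228)/2 = 0.470. It would show the same if both arms were at 0.470, again with no benefit in B.

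The same correlation therefore fits a 48-point benefit and none at all.

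**2. How often the link appears.** Logistic simulation of the first case (B purely prognostic, common odds ratio 8.35), 2,000 trials for each share of B:

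| Test at 5% | B in 25% | B in 50% |
|---|---|---|
| B linked to worse outcome, MUA patients only | 52% | 60% |
| B linked to worse outcome, arms pooled | 75% | 85% |
| Arm-by-lesion interaction | 4.7% | 5.6% |
| MUA against injection within B | 99% | 100% |

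Check of the 60% by formula, 72 per class: difference 0.1506; null SE √(0.7867 × 0.2133 × 2/72) = 0.0683; alternative SE 0.0671; (0.1506 − 1.96 × 0.0683)/0.0671 = 0.25, giving 60%.

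In the first two rows the test is right about prognosis. The error lies in reading the result as unsuitability for MUA.

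**3. Between-arm subgroup comparisons.** The last row shows that these avoid the prognostic error. They do not test whether the effect in B differs from that in A. If many classes are examined, chance enters. As written, the Ellman scheme has 3 × 3 + 4 × 4 = 25 type-by-grade cells. If all were used and evenly filled, there would be 144/25 = 5.76 patients per arm per cell, about 32% power at the full 43.4-point difference, and 1 − 0.95²⁵ = 72% chance of at least one false positive over 25 independent tests. This is the upper extreme, not something the protocol says it will do.

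**4. What the interaction can deliver.** At the planning rates, v = 0.862 × 0.138 + 0.428 × 0.572 = 0.364. The main effect has a 95% half-width of 1.96√(v/144) = 9.9 points. With two equal classes, the difference between class effects has 1.96√(v/72 + v/72) = 19.7 points, twice as wide. With a 25/75 split it is 1.96√(v/36 + v/108) = 22.8 points. By simulation, interaction power is 95–99% if MUA has no effect in B, and 43–49% if the log odds ratio in B is halved (B with the same control rate as A). Coarse classes are feasible for a large contrast; moderate ones would often be missed.

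**The case against.** The strongest reply is that the defect is read from silence. The article rejects no interaction. It lists logistic regression, which can carry a product term, and the terms of such a model commonly sit in an analysis plan that is not shown. It uses both randomised arms, and subgroup analysis in a two-arm trial ordinarily means comparing the arms within a subgroup. The work is an additional analysis and leaves the primary comparison untouched.

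Much of this stands, and it rules out several stronger readings that a reader might infer:
- *That the plan uses correlation in place of an interaction, so lesions will be mislabelled.* The text permits between-arm subgroup comparisons and product terms. Mislabelling is possible, not certain: it needs lesions to be prognostic and suitability to be read from MUA patients or a pooled correlation.
- *That item 1.2 conditions on the 24-week grade.* The reference to imaging before and after treatment covers all three items, and item 1.3 needs the later image. Nothing says that item 1.2 uses it to define classes.
- *That all 25 Ellman cells will be tested.* The scheme is given as the way to read the MRI. Item 1.2 speaks only of type and degree, and coarse classes fit that wording equally well.

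The reply does not remove the point. The article is not silent on method: it names correlation as the framework, states a question about differential benefit, and says that the one will settle the other. Under the correlation reading the answer can be wrong. Under the subgroup reading there is no test that effects differ. Neither supports the word *determined*.

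**Conclusion.** The point holds in this limited form. Item 1.2 poses a question of differential benefit, and the framework named for it does not by itself answer that question, so a lesion with poor prognosis under either treatment can be reported as unsuitable for MUA. In the illustration the raw material for that error (a significant lesion-outcome link with undiminished benefit) arises in 52–85% of trials, against about 5% for the interaction test. Those percentages rest on an assumed lesion share, an assumed 20-point prognostic gap, a common odds ratio, and tests chosen to represent the correlation reading. They are not error rates of the planned analysis. The identification argument in step 1 of the working needs none of the simulated figures. The primary comparison is unaffected. A change of wording is worth making because item 1.2 bears directly on who is offered MUA.

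**What to change.** Rewrite item 1.2 as a model with arm, baseline lesion class, arm-by-class interaction and site.
- Define class from the pre-treatment MRI only, in a few categories fixed in advance (for example no tear, partial thickness, full thickness).
- Report the MUA-minus-injection difference with its 95% confidence interval in each class, and the interaction test.
- Label the analysis exploratory and replace *determined* with *explored*.

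No new data, visits or patients are needed. The cost is a weaker claim: interaction estimates are less precise than the main effect (about twice as wide with two equal classes), so the trial could suggest, but seldom settle, which lesions benefit less.

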## Objectives {7}

The objective of this trial is to observe the safety and efficacy of MUA, compared to intra-articular steroid injection, in the treatment of FS patients diagnosed with rotator cuff injury or tear by MRI. We hypothesize that the course of the disease can be shortened by MUA with quicker functional recovery and gain in the range of motion and a subsequent faster return to work compared to steroid injection treatment. Also, preoperative and sequent MRI and musculoskeletal ultrasounds will be applied to patients before and 6 months post the intervention to evaluate the condition of the patient’s rotator cuff injury or tear.

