##### Control group: intra-articular steroid injection

The intra-articular steroid injection procedure are as follows: Thoroughly sterilize the affected shoulder, inject 2 ml of chitosan and 2.5 ml of Diprospan diluent into the posterolateral approach of the shoulder joint cavity, and inject 2.5 ml Diprospan into the supraspinatus tendon, subacromial bursa, and long head of biceps tendon, respectively.

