##### Post-procedural physiotherapy (PPP)

Patients from both groups will initiate a 14-day functional exercise, starting on the first day after the intervention treatment. A uniformly and strictly trained physician guides the first functional exercise of the patients until the patients and their accompanying family members have mastered the correct exercise method. They can record relevant videos, and family members can assist and supervise patients in the initial exercise stage. Physicians follow up with patients regularly to ensure the standardization and correctness of exercise posture.

The specific methods are as follows:①Forward elevation: The patient stands facing a wall with their feet shoulder-width apart and toes touching the wall. The fingers of the affected arm are spread out and placed on the wall. Slowly elevate the arm along the wall until the limit of pain tolerance is reached. The unaffected arm can assist in lifting the affected arm, or another person can push the scapula of the affected side from behind to help raise the arm to the maximum position.②Forward flexion with shoulder support: The affected shoulder is flexed to 90° with the elbow flexed. The palm of the unaffected hand is gradually placed on the elbow, moving it towards the midline to bring the affected arm to rest on the opposite shoulder joint.③Extension with internal rotation: The patient sits or stands with the palm of the affected hand facing backward and extends the shoulder joint. Within the limit of pain tolerance, gradually rotate and adduct the affected arm while bending the elbow until the fingers touch the opposite scapula. The unaffected hand can assist the affected hand in completing the exercise.

Repeat the above movements after the patient’s pain is relieved. Perform three sets of each exercise, three times per day.

The ROM, CMS, MPQ, VAS, and PPI numbers or scores will be collected at 1 day, 2 weeks, 4 weeks, 12 weeks, and 24 weeks after the intervention. Additionally, imaging examinations will be conducted during the 24-week visit. Due to the nature of the physical examinations required, all follow-up time points must be completed by the patients at the hospital’s outpatient or inpatient departments.

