##### Safety evaluation

Adverse effects, including humeral shaft fracture, glenoid fracture, shoulder dislocation, complex regional pain syndrome, neurovascular lesions, and infection, will be recorded at any time during the trial. In addition, an MRI of the glenohumeral joint and a musculoskeletal ultrasound of the shoulder will be performed 6 months after treatment to assess the safety effects of the MUA on the rotator cuff.

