## Discussion

In this study, we propose to compare the efficacy of manipulation under anesthesia versus intra-articular steroid injection in the treatment of patients diagnosed with rotator cuff injury with frozen shoulder. We expect that the MUA group will have a superior outcome compared to the intra-articular steroid injection group in terms of the primary outcome measure. If our hypothesis is confirmed, this study could lead to a change in the standard of care for patients with rotator cuff injury and frozen shoulder and provide a new treatment option with fewer side effects and better outcomes.

It is important to note that this study has several limitations. First, the study is single-blinded due to the nature of the interventions, meaning that the physicians will not be blinded to the treatment group, which could introduce bias. Second, the study is limited to patients diagnosed with rotator cuff injury with frozen shoulder based on MRI findings and may not be generalizable to patients with other types of shoulder injuries. Finally, the study is limited to 24 weeks of follow-up, and longer-term outcomes are not evaluated.

In conclusion, this study protocol outlines a randomized controlled trial that will compare the efficacy of manipulation under anesthesia versus intra-articular steroid injection in the treatment of patients diagnosed with rotator cuff injury with frozen shoulder. The study has the potential to provide important insights into the treatment of this common condition and could lead to improvements in patient care.

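### The cuff-safety question is worded as change after MUA with no comparator and a promise to verify safety; it should be the randomised contrast that the scheduled images already allow

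*Protocol article*

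**What the plan says.** Item 1.3 of Additional analyses {20b} is to determine whether "there is an increase in the degree of rotator cuff injury after MUA and to verify the safety of MUA" in patients with rotator cuff injury. Under Outcomes {12}, Safety evaluation, MRI and ultrasound 6 months after treatment are done "to assess the safety effects of the MUA on the rotator cuff". Both statements mention MUA only.

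Other sections are comparative or cover both arms:

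- Objectives {7}: "The objective of this trial is to observe the safety and efficacy of MUA, compared to intra-articular steroid injection". The same paragraph says that MRI and "musculoskeletal ultrasounds will be applied to patients before and 6 months post the intervention", with no restriction to one arm.
- Post-procedural physiotherapy, which applies to both groups: "imaging examinations will be conducted during the 24-week visit". Table 1 also schedules imaging at screening and at 24 weeks.
- Additional analyses {20b} opens by drawing on MRI and "musculoskeletal ultrasound imaging data before and after treatment of a total of 320 patients collected in the study", to be analysed by subgroup analysis, sensitivity analysis and logistic regression.
- Statistical methods, Outcomes {20a}, gives MUA-to-injection rate ratios for complications, a list that includes tendon injury.

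No section states that change in imaging grade (Ellman, Goutallier or Thomazeau) is compared between the arms, and none states an acceptable excess of cuff worsening.

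**The concern.** The Background gives fear of further cuff tearing as the reason many physicians withhold MUA from these patients. Whether MUA worsens the cuff is therefore the safety question that matters most here. A change observed after MUA has at least three possible sources: the manipulation, 24 weeks in the life of a lesion that the Background calls chronic, and grading that drifts in one direction when later scans are compared with earlier ones. Only the randomised control arm separates the first from the other two.

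The wording can fail in two ways. Natural worsening may be attributed to MUA. Or a non-significant change may be reported as confirming safety, when the data would still allow an excess that clinicians would care about.

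**Working it through.** **Inputs.** From Sample size {14}: 160 per arm and 10% dropout, so 160 × 0.9 = 144 evaluable per arm; two-sided alpha 0.05. The protocol states no figure for the cuff question, so there is none to reproduce. It also gives no rate of cuff progression or misgrading over 24 weeks. The rates below are assumptions, shown as a range.

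**1. The question as worded: change within the MUA arm, with no MUA effect.** Let w be the probability of being graded worse at 24 weeks and b of being graded better, both unrelated to treatment. The number of changed shoulders is K ~ Binomial(144, w + b). Given K, the number worse is Binomial(K, w/(w + b)), tested against one half by an exact two-sided sign test. The probability of a significant increase is:

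| Graded worse | Graded better | Significant increase |
|---|---|---|
| 5% | 5% | 1% |
| 10% | 5% | 27% |
| 10% | 3% | 59% |
| 10% | 2% | 77% |

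For the third row, about 144 × 0.13 = 18.7 shoulders change grade, 14.4 worse and 4.3 better. With 19 changed, 15 or more worse is significant. The first row shows that symmetric misgrading alone does not produce false harm; net worsening or directional grading is needed. The sign test is my illustration of a before-after answer. The protocol does not name it.

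**2. What a non-significant result can show, even between arms.** Take 144 per arm and true worsening of 5% versus 10%.

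- Mean proportion: 0.075.
- Standard error under no difference: √(2 × 0.075 × 0.925 / 144) = 0.03104.
- Standard error under the alternative: √((0.05 × 0.95 + 0.10 × 0.90) / 144) = 0.03090.
- Power: Φ((0.05 − 1.96 × 0.03104) / 0.03090) = Φ(−0.351) = 0.36.

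A doubling from 10% to 20% would be detected with 66% power.

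**3. Precision of the between-arm difference.** With 10% worsening in both arms, the 95% half-width is 1.96 × √(2 × 0.10 × 0.90 / 144) = 0.069, or 6.9 points. At 5% in both arms it is 5.0 points, and at 20% it is 9.2.

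**4. What the trial could exclude.** With n per arm = (1.96 + 0.8416)² × 2 × p(1 − p) / m², p = 10% in both arms and 80% power, excluding an excess of m = 10 points needs 142 per arm, and excluding 5 points needs 566. These margins are illustrative only.

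**The case against.** The strongest reply is that no one-arm test is specified. Section {20b} starts from imaging in all 320 patients and names logistic regression, which can carry a treatment term. The trial objective is comparative, and {20a} summarises outcomes by group and promises 95% intervals for all treatment effects. This stands in part. A reader might infer that the protocol has committed to a before-after test in the MUA arm, or that its analysis cannot separate MUA from time. The documents do not support that; they support only that the question is worded without a comparator. But the logistic regression is introduced as part of a correlation analysis, the rate ratios count complications and not change in imaging grade, and no treatment effect on grade is defined anywhere.

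A second reply is that this is an additional, unpowered analysis whose details belong in an analysis plan. That is fair for the definition of worsening, the handling of site and the choice of interval method, and low power is expected. It does not excuse the stated aim of verifying safety, which such an analysis cannot meet without a stated limit.

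Two further inferences should be resisted. Grading error as such is not read as harm, as the 1% row shows. And the Discussion's hope that MUA may "provide a new treatment option with fewer side effects and better outcomes" is conditional prose, not an analysis rule, so it has no bearing on how the images will be analysed.

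**Conclusion.** The point holds as a mismatch between the cuff-safety question and both the trial's own objective and the data it will hold. Both misreadings are risks created by the wording; the protocol does not say that either will happen. The false-harm risk runs from about 1% to 77% over the scenarios shown and depends wholly on the assumed net worsening, so no single figure should be quoted alone. The limit on claiming safety is firmer: across equal rates of 5% to 20%, the between-arm interval is about ±5 to ±9 points with 144 per arm, so a non-significant result is not verification. This should be changed, but it does not affect the primary efficacy analysis.

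**What to change.** - Restate item 1.3 as the difference, MUA minus injection, in the proportion of patients whose cuff grade is worse at 24 weeks than at baseline, with a 95% confidence interval and each arm's own proportion. Align the Safety evaluation sentence with it.
- Say that the already designated MRI reader is kept unaware of arm. The abstract promises blinded outcome assessors, but {20b} does not say this of the reader.
- Replace the aim of verifying safety with this estimate and its interval. If that aim is kept, state the excess to be excluded before the allocation code is opened.
- Note in the interpretation that the comparator also acts on the cuff ("inject 2.5 ml Diprospan into the supraspinatus tendon"). The contrast is relative to that treatment and not to an untouched cuff.

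The cost is one further analysis of images already scheduled and a more cautious safety claim. No extra patients or scans are needed.
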